15 APPENDICES LIST …………………………………………………………………………………………………………..……….33

LIST OF ABBREVIATIONS

| AE | Adverse Event/Adverse Experience |
| --- | --- |
| CONSORT | Consolidated Standards of Reporting Trials |
| CRF | Case Report Form |
| CPLE | *Carica papaya* leaf extract |
| GCP | Good Clinical Practice |
| ICF | Informed Consent Form |
| ICH | International Conference on Harmonization |
| IRB | Institutional Review Board |
| LFT | Liver Function Tests |
| AST | Aspartate Aminotransferase |
| ALT | Alanine Aminotransferase |
| MOP | Manual of Procedures |
| N | Number (typically refers to subjects) |
| PI | Principal Investigator |
| SAE | Serious Adverse Event/Serious Adverse Experience |
| SOP | Standard Operating Procedure |
| UP | Unanticipated Problem |
| WHO | World Health Organization |

PROTOCOL SUMMARY

| **Title:** | A prospective study to evaluate the safety and efficacy of *Carica papaya* leaf extract (oral CPLE (Caripill)) in the treatment of severe thrombocytopenia (≤30,000/µl) in dengue |
| --- | --- |
| **Précis:** | This will be a placebo-controlled, single center, randomized prospective study of CPLE (Caripill) (*Carica papaya* leaf extract) tabs in dengue patients with severe thrombocytopenia (platelets ≤ 30,000/ul). The study will enroll 100 eligible dengue cases into the two arms of the study – one arm receiving CPLE (Caripill) 1100mg *t.i.d* for 5 days and the other group receiving placebo. |
| **Objectives:** | Primary: To determine the impact of CPLE (Caripill) administration (1100mg *t.i.d* for 5 days on the following:   - Platelet count and hematocrit values in dengue patients with severe thrombocytopenia. - Reducing the number of blood product transfusions *esp.* platelet transfusion and - All-cause mortality rates. |
|  | Secondary: To evaluate the effect of CPLE (Caripill) administration (1100mg *t.i.d* for 5 days) on the following-   - Magnitude and kinetics of serum viremia (or NS1 antigenemia). - Magnitude and kinetics of cytokines IFNγ, IL6, TNFα and IL4. - The total length of hospital (ICU & ward) stay, |
| **Population:** | Study cohort of 100 adults, either gender (more than 18 yrs old, non-pregnant) and admitted to AIMS Hospital and diagnosed of dengue with moderate to severe thrombocytopenia. |
| **Number of Sites:** | Dept. of General Medicine and Dept. of Emergency Medicine, Amrita Institute of Medical Sciences and Research Center, [name]. |
| **Description of Intervention:** | Orally available CPLE (Caripill) Tabs (Micro Labs Ltd) at a dose of 1100 mg/tab three times a day for 5 days |
| **Study Duration:** | The estimated time (in months) from when the study opens to enrollment until completion of data analyses will be 12 months. |
| **Subject Participation Duration:** | Duration of hospital stay and the subsequent follow-up at 2 week post last dose of CPLE (Caripill). |
| **Estimated Time to Complete Enrollment:** | Immediately after screening positive and signing the informed consent form (ICF). |

**Schematic of Study Design**

For 50 cases: Obtain informed consent. Screen potential subjects by inclusion and exclusion criteria; obtain history and fill in the Clinical Research Form (CRF).

**Randomization**

**Treatment Group (N=50)**

**Control Group (N=50)**

**Day 0**

Clinical examination and detailed biochemical, hematological and virological laboratory investigations will be performed at baseline. Peripheral blood (5ml) will be collected; CRF will be completed for each enrolled subject. Administer CPLE (Caripill) or placebo *t.i.d* for 5 days.

Repeat study intervention (*if applicable*).

Follow-up assessments of study endpoints and safety. Appropriate recommended “standard of care” treatment modalities will be employed for each study subject. Routine hematological and biochemical laboratory assays will be done. Administer CPLE (Caripill) or placebo *t.i.d* for 4 more days.

**Day 1**

Follow-up assessments of study endpoints and safety. Appropriate recommended ‘standard of care” treatment modalities will be employed for each study subject. Routine hematological, biochemical and virological laboratory assays will be done. Administration of CPLE (Caripill) or placebo *t.i.d* will continue.

**Day 2**

Follow-up assessments of study endpoints and safety. Appropriate recommended ‘standard of care” treatment modalities will be employed for each study subject. Routine hematological and biochemical laboratory assays will be done. Administration of CPLE (Caripill) or placebo *t.i.d* will continue.

**Day 3**

Follow-up assessments of study endpoints and safety. Appropriate recommended ‘standard of care” treatment modalities will be employed for each study subject. Routine hematological and biochemical laboratory assays will be done. Administration of CPLE (Caripill) or placebo *t.i.d* will continue

**Day 4**

Final assessments of study endpoints and safety. Appropriate recommended ‘standard of care” treatment modalities will be employed for each study subject. Routine hematological and biochemical laboratory assays will be done. Administration of final dose of CPLE (Caripill) or placebo *t.i.d* continue

**Day 5**

Follow up assessments will occur at 2 week interval after the final dose of CPLE (Caripill) or placebo tab including the routine clinical, biochemical, hematological assays.

1. INTRODUCTION: BACKGROUND INFORMATION AND SCIENTIFIC RATIONALE
   1. Background Information

Dengue is a mosquito borne flavivirus infection that occurs in the tropical and sub-tropical regions of the world. World Health Organization (WHO) lists dengue among one of the seventeen prioritized, neglected tropical diseases that affects more than a billion populations. According to its most recent epidemiological data, dengue has a yearly incidence of about 50-100 million cases, with 40% of the global population considered at risk for dengue^1^. As the vector habitat expands, dengue outbreaks have become a common occurrence in Asia, especially India. Recent data from WHO reports the case fatality rate of dengue at 2.5% and the estimated morbidity and mortality due to dengue infection as approximately 1,300 disability-adjusted life years (DALYs) per million^2^. These figures clearly highlight the severe impact dengue infection can have on the public healthcare costs and resources. In India, dengue is endemic or hyperendemic in most parts and the healthcare and economic cost of regular and isolated outbreaks can be very high as estimated in the recent study by *Shepard et al*^3^.

Dengue is known to be heterogeneous in its clinical presentation and the unpredictable nature of its severity and outcomes often proves to be a challenge to the clinician. While a majority of dengue infections resolve rapidly after presenting as mild asymptomatic febrile illness, a small percentage of dengue infected cases progress to severe disease characterized by excessive bleeding and plasma leakage that can eventually lead to shock (DSS) and death. Management of dengue is largely based on providing timely, appropriate and supportive treatment. In order to facilitate early diagnosis and timely management of severe dengue, the WHO in 2009 introduced a new set of criteria for its clinical classification based on its severity. Based on clinical severity criteria, dengue cases are now categorized as ‘dengue with’ or ‘dengue without’ warning signs and severe dengue^5^.

**Dengue and Thrombocytopenia**

Thrombocytopenia, marked by a platelet count less than 150,000/µl of blood, is one of the hallmark indicators of severity in dengue viral infections. Typically platelet counts decline steeply during the infection within the initial 4-6 days of onset of fever and revert back to normal levels in the consequent days as the fever subsides. During the phase of defervescence, plasma leakage due to increased vascular permeability could potentially exacerbate the condition, leading to life threatening dengue shock syndrome (DSS) in patients with hemorrhagic fever (DHF) ^6^. Previous studies have reported an association between depleted platelet levels and higher prevalence of clinical bleeding in patients with dengue viral infections^7^. Inadequate platelet levels that fail to suppress bleeding and initiate coagulation could also lead to the bleeding symptoms. One of the several mechanisms proposed to explain thrombocytopenia during the infection of DENV serotypes involves the inhibition of bone marrow progenitor cell proliferation and functions^8^. Decline of megakaryocyte progenitors in the bone marrow has been demonstrated during dengue viral infection in humanized mice, possibly indicating the suppression of platelet production leading to dengue induced thrombocytopenia^9^. Depletion of platelets during dengue viral infection can also be attributed to the activated immune response that destroys platelets by augmented apoptosis, lysis and antibodies^10^. The non-structural protein NS1 is expressed in infected cells, eliciting immune responses. DENV infections also lead to up-regulation of membrane bound Tissue Factor (TF) and activation of platelets. Coagulation and inflammatory pathways are initiated, leading to the release of pro-inflammatory cytokines like TNF-α and IL-6. Raised levels of TNF-α has been associated with hemorrhagic symptoms. Moreover, immune dysregulation can also lead to alterations in platelets functions. Plasma leakage from capillaries has also been associated to altered platelet functions^11^ Endothelial sequestration is another mechanism that leads to thrombocytopenia. Platelets increasingly attach to von-Willebrand factor (vWF) on vascular endothelial cells, resulting in small clogs in microcirculation and low levels of platelets in the peripheral blood^12^.

Management of thrombocytopenia in dengue using platelet transfusions have met with no significant improvements in relation to bleeding and was associated with increased length of hospitalization and side effects. According to the Dengue Fever management guidelines recommended by the Dept of Health, Govt. of Kerala, platelet transfusions are not advisable in the absence of bleeding. Platelet transfusions are to be initiated only when platelet counts are <10,000 without bleed or platelet count <50,000 with bleeding^13^. This clearly suggests that management of thrombocytopenia in severe dengue cases is a challenge. Prophylactic transfusions are also currently discouraged by W.H.O^14^.

***Carica papaya* leaf extract. (CPLE) and its role in dengue associated thrombocytopenia**

The anti- inflammatory, anti-tumor and anti-bacterial effects of *Carica papaya* leaf extracts have been demonstrated in several studies^15-17^. Traditionally it has been also used in many countries as an anti-pyretic. *Carica papaya* is rich in alkaloids, saponins, flavonoids, tannins and glycosides that mediate its various biological activities. *Caricapapaya* leaves are rich in cardiac glycosides, anthraquinones, carpaine, pseudocarpaine, and other phenolic compounds^18-19^. Previous studies on papaya leaves have shown that seed extract of *C.papaya* possesses pharmacological activities, including anthelminthic, antifertility, contraceptive etc. A hot-water extract of the leaves is taken orally as an anti-pyretic, and in the treatment of anemia and appetite stimulation^19, 20^. It is also effectively used as a natural remedy to treat dengue fever associated with thrombocytopenia^19^. *In vitro* hemolytic studies have shown that CPLE has erythrocyte stabilization potential and thereby prevent hemolysis^21^. *In-silico* energy binding studies using bioinformatic tools have indicated that flavanoid quercetin from *Carica papaya* could potentially inhibit the NS2B-NS3 protease which are required for viral assembly. This however, has yet to be confirmed experimentally^22^. A toxicity study conducted in Sprague-Dawley rats revealed that oral administration of *Carica papaya* leaves juice (CPLJ) was not safe ^23, 24^.

Other murine studies have also reported a platelet and RBC increasing effect with administration of leaf extracts of *Carica papaya*^25, 26^. A similar study by *Hettige et al* performed in Sri Lanka confirmed a significant increase in the platelet as well as the leukocyte count^27^. *Subenthiran S et al* showed that *Carica papaya* leaves juice (CPLJ) significantly accelerates the rate of increase in platelet count in patients with dengue fever and DHF^28^. They also report a significant increase in the expression levels of ALOX 12 and PTAFR genes in the interventional group compared to those who received just the standard treatment. Both these genes play a major role in hematopoiesis^29, 30^.

**Clinical trials of *Carica papaya* leaf extract (Oral CPLE (Caripill)) in Dengue**

More recently, a clinical study performed in Rajasthan, India on 400 dengue patients with thrombocytopenia (platelet <150,000/µl), assessing the effect of CPLE on the platelet counts concluded that administration of CPLE increased the platelet count without any side effects and/or complications otherwise associated with thrombocytopenia. Additionally, it was also noted that there was a decrease in the length of hospital stay as well as significant reduction in the need for platelet transfusions for dengue patients on CPLE tabs^31^. Another recent large, multicentric, double blind, placebo-controlled, randomized trial evaluating the efficacy and safety of CPLE (Oral Caripill) as an empirical therapy for thrombocytopenia with a platelet count of 30,000 – 100,000/µl in dengue patients showed excellent results. Patients in the treatment group had significant increase in the platelet count over the therapy duration. With very few adverse events recorded in the treatment group, Caripill was demonstrated to be safe and efficacious for the studied indication^32^. These evidences strongly suggest the benefits of *Carica papaya* leaf extract in the management of dengue related thrombocytopenia. However, the beneficial role of CPLE is still not been evaluated in the management of severe thrombocytopenia (< 30,000/µl) especially in cases where platelet transfusions are warranted. Also, while the literature is rich in *in-vitro*, preclinical and clinical effects of *Carica papaya* leaf extract on the platelet count, not much is evidences are available on the mechanistic basis of this effect. There is also not much evidence on the direct antiviral effect of *Carica papaya* leaf extract. In both the trial studies, observational data is not available on the viral load, kinetics or infection induced inflammation.

- 1. Rationale

There is no available antiviral therapeutic against dengue illness. Dengue fever management is mostly symptomatic and measures are usually target the management of severe symptoms including thrombocytopenia. With the hyperendemicity of dengue infection in India, and crunch due to supply and demand mismatch of platelet transfusions in our resource limited setting, research into availability of a cost effective alternative treatment modality of dengue associated severe thrombocytopenia is the need of the hour. In the light of growing body of in-vitro, preclinical and clinical studies evaluate the efficacy of *Carica papaya* leaf extract (CPLE) in improving the platelet numbers in peripheral circulation in mild and moderate dengue, we also aimed to estimate the efficacy and safety of CPLE (Caripill tabs) in increasing the platelet count in severe dengue, classified as per the WHO 2009 guidelines. CPLE as Caripill was chosen as the study drug for both scientific and pragmatic reasons. Recent evidences confirmed the safety and tolerability of CPLE when administered as Caripill tabs in dengue patients reduce incidence of side effect. CPLE both as generic and as Caripill tabs and will therefore be immediately available to patients if there is a positive result from the trial.

- 1. Potential Risks and Benefits
     1. Potential Risks
- No serious risks are anticipated for this product. Preclinical and pilot clinical studies have well established the safety of Caripill for human use. C. papaya leaf extract at a dose of up to 2000mg/kg body weight in rats was safe indicating that in human, a dose of up to 19 g of C. papaya leaf extract would be safe. Preclinical sub-acute oral toxicity studies on Sprague-Dawley rats showed that C. papaya leaf extract at a dose up to fourteen times the levels employed in practical use in traditional medicine could be considered safe as a medicinal agent^23-25^.
- The detailed product information (Product Monograph) is provided as Supplement (Appendix III).
- As mentioned in the product monograph, CPLE is contraindicated in males with prostate dysfunction (ie, BPH or prostate cancer); C. papaya should be avoided as it increases the iron absorption. Excess iron may increase oxidative stress, especially in the aging male. Iron overload may increase the risk of developing prostate cancer. Caripill should be used with caution in individuals with bleeding disorders or those taking blood thinning medications such as aspirin or warfarin. In view of this, to ensure patient safety, we will be excluding these patients.
- Patients will be monitored for any liver impairment. Routine biochemical, LFTs (Liver function tests) including serum albumin levels will be monitored on a daily basis. These parameters will be monitored throughout the study period i.e including the hospital stay and follow-up visits.

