1. STUDY ENROLLMENT AND WITHDRAWAL

Adult (≥ 18yrs) patients admitted to the Amrita Institute of Medical Sciences and Research Center and meeting all the inclusion and exclusion screening criteria of the study will be enrolled once signed informed consent is obtained. A total of 100 cases of dengue with a thrombocytopenia (peripheral platelet count of ≤30,000/µL) will be enrolled into the two arms of the study. The point of enrollment is defined as the time at which a patient has signed and dated the consent form.

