**5.1 Subject Inclusion Criteria**

In order to be eligible to participate in this study, an individual must meet all of the following criteria:

1. Provide signed and dated informed consent form
2. Willing to comply with all study procedures and be available for the duration of the study
3. Male or female, aged ≥ 18 yrs of age. Clinically diagnosed of dengue and a peripheral platelet count of ≤30,000/µL.
4. A laboratory positive diagnosis of dengue confirmed by a positive NS1 or IgM or IgG ELISA test and/or detection of viral RNA by real time PCR assay.

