**5.2** **Subject Exclusion Criteria**

Patients with one or more of the following criteria at enrolment will be excluded from the study:

- 1. Pregnancy and lactation.
  2. Patients who has been given steroids for thrombocytopenia and also those who have been transfused platelets before starting the drug
  3. Taking indigenous medicines.
  4. Alanine aminotransferase (ALT) >150 U/L

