**5.5 Subject Withdrawal**

Subjects may withdraw voluntarily from the study or the investigator may terminate a subject's participation if:-

- Any clinical adverse event (AE), laboratory abnormality, or other medical condition or situation occurs such that continued participation in the study would not be in the best interest of the subject.
- The subject meets an exclusion criterion (either newly developed or not previously recognized) that precludes further study participation.
  1. Premature Termination or Suspension of Study

This study may be suspended or prematurely terminated if there is sufficient reasonable cause. Written notification, documenting the reason for study suspension or termination, will be provided by the P.I.s If the study is prematurely terminated or suspended, the principal investigator will promptly inform the IRB and will provide the reason(s) for the termination or suspension.

Circumstances that may warrant termination include, but are not limited to:

- Determination of unexpected, significant, or unacceptable risk to subjects.
- Insufficient adherence to protocol requirements.
- Data that is not sufficiently complete and/or evaluable.
- Determination of futility.

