1. STUDY INTERVENTION
   1. Study Product Description

Package Insert information on CPLE (Caripill) tabs

- - 1. Acquisition

CPLE (Caripill) and placebo tablets will be supplied by MicroLabs Ltd.

- - 1. Formulation, Packaging, and Labeling

Packaging and labeling of CPLE (Caripill)

- - 1. Product Storage and Stability

The CPLE (Caripill) tabs will be stored at room temperature, away from heat and direct light.

- 1. Dosage, Preparation and Administration of Study Product

CPLE (Caripill) and placebo tabs of 1100mg in strength will be administered orally three times a day for 5 days.

- 1. Assessment of Subject Compliance with Study Product Administration

Each study subject will be directly observed for patient compliance by pill counts by the study nurse co-ordinator.

- 1. Concomitant Medications/Treatments

The treatment plans including the details of the concomitant medications will be recorded in the case record form (CRFs – Appendix I).

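### The three patient groups that the risk section says will be excluded do not appear in the exclusion criteria of Section 5.2

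*Protocol*

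**What the plan says.** Section 2.3.1 (Potential Risks) draws on the product monograph. It states that "CPLE is contraindicated in males with prostate dysfunction (ie, BPH or prostate cancer"), giving increased iron absorption as the reason. It continues: "Caripill should be used with caution in individuals with bleeding disorders or those taking blood thinning medications such as aspirin or warfarin". The paragraph closes with the commitment "In view of this, to ensure patient safety, we will be excluding these patients".

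Section 5.2 is the list that would carry out this commitment. It opens with "Patients with one or more of the following criteria at enrolment will be excluded from the study" and gives four items:

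1. pregnancy or breast-feeding;
2. steroids given for thrombocytopenia, or platelets transfused, before the study drug;
3. use of indigenous medicines;
4. ALT above 150 U/L.

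On sex and age, Section 5.1 requires only "Male or female, aged ≥ 18 yrs of age". The introduction to Section 5 says that patients "meeting all the inclusion and exclusion screening criteria of the study will be enrolled once signed informed consent is obtained".

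**The concern.** The risk section tells an ethics committee or a safety reader that a safeguard exists, but the list used to decide who enters the trial does not contain it. Two things are at stake.

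First, a man with a condition that the protocol itself calls a contraindication could be enrolled without breaching any listed criterion.

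Second, the caution about bleeding disorders and blood thinners bears directly on this population. Every patient enters with platelets at or below 30,000/µL, and the incidence of bleeding is one of the primary objectives.

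The concern is about patient safety and about the protocol agreeing with itself. It is not a claim that the efficacy comparison would be biased.

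**Working it through.** No figure in the plan needs reproducing. The check sets the three groups named in Section 2.3.1 against every visible part of the protocol that could keep them out.

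| Place in the protocol | Prostate disease | Bleeding disorder | Blood thinners |
|---|---|---|---|
| 2.3.1 Potential Risks | contraindicated | caution | caution |
| 5.1 Inclusion (4 criteria) | not named | not named | not named |
| 5.2 Exclusion (4 criteria) | not named | not named | not named |
| 6 Concomitant Medications | not addressed | not addressed | recorded, not barred |
| 5.5 Withdrawal | only if an exclusion criterion | only if an exclusion criterion | only if an exclusion criterion |

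**Count.** Criteria naming any of the three groups: 0 of 4 in Section 5.1 and 0 of 4 in Section 5.2.

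**Could an existing item cover a group indirectly?**
- The item on indigenous medicines does not reach aspirin or warfarin.
- The item on earlier steroids or platelet transfusion concerns treatment already given, not an underlying bleeding disorder.
- The ALT limit and the pregnancy item are unrelated to all three groups.
- Section 5.1 sets no upper age limit, so older men can qualify.

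**Could another section close the gap?**
- Section 6 says of other drugs only that "The treatment plans including the details of the concomitant medications will be recorded in the case record form".
- One withdrawal ground in Section 5.5 is "The subject meets an exclusion criterion (either newly developed or not previously recognized) that precludes further study participation". It helps only if the condition counts as an exclusion criterion.
- The other ground in Section 5.5 concerns the subject's best interest. It is discretionary and acts after enrolment.
- The screening text in Section 7 refers to the study's inclusion and exclusion criteria and points to the Schedule of Events (Appendix IV) for details. That appendix and the CRF (Appendix I) are not shown. Section 5.2 itself points to no further criteria elsewhere.

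**Exposure of one such patient.** Under 1:1 allocation the chance of active drug is 1/2. On the three-times-daily regimen in Section 6, 3 tablets/day × 5 days = 15 tablets, and 15 × 1100 mg = 16,500 mg = 16.5 g over the course, or 3.3 g per day. These figures describe exposure only and do not measure harm.

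**The case against.** The best defence is that Section 2.3.1 is itself protocol text and its commitment is unconditional. The introduction to Section 5 and the withdrawal rule in 5.5 speak of exclusion criteria without citing 5.2. A careful reader could therefore treat the three groups as excluded already, with the list merely incomplete. This is a fair account of what the authors probably meant. It does not remove the fault, because 5.2 is headed and introduced as the list of exclusions, and staff working from it would not see these groups.

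A second point is that the Schedule of Events and the CRF may carry the items. They may, and what happens in practice depends partly on them. Even so, 2.3.1 and 5.2 would still disagree.

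Third, the closing sentence of 2.3.1 might refer only to the two caution groups that it directly follows. That reading is possible. However, 5.2 omits those two groups as well, so the contradiction survives. On that reading the men with a contraindication are excluded nowhere in the visible text, which is no better.

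Fourth, the size of the harm is not shown. Two of the three groups carry only a caution. The prostate warning rests on iron overload, which the protocol does not quantify for a five-day course. Section 2.3.1 also regards up to 19 g of extract as safe in humans, against 3.3 g per day here. This stands as a limit on what can be claimed. It does not justify leaving out an exclusion that the protocol has already promised on safety grounds.

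**Conclusion.** The point holds and should be corrected. None of the three groups that Section 2.3.1 marks out is named in the four exclusions of Section 5.2 or the four inclusions of Section 5.1, and no other visible section keeps them out before enrolment. Screening on those lists as written can randomise patients whom the protocol says it excludes to ensure their safety.

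How many patients this would affect cannot be derived, because the protocol gives no prevalence for any of the groups. The conclusion assumes that 5.2 is the operative list and takes the broader, more likely reading of the commitment in 2.3.1; the narrower reading leaves 5.2 equally inconsistent. What the unseen appendices contain could change practice at the site, but not the disagreement between the two sections.

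**What to change.** Keep the commitment in Section 2.3.1 and add three numbered exclusions to Section 5.2, repeated on the screening form:

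- (a) benign prostatic hyperplasia or prostate cancer;
- (b) a known bleeding disorder that pre-dates the present dengue illness, with a statement that thrombocytopenia or bleeding due to dengue does not exclude;
- (c) current use of an anticoagulant or antiplatelet drug, such as warfarin or aspirin.

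The qualification in (b) is needed because low platelets and dengue-related bleeding define or accompany the condition under study. Once the three items are listed, the existing withdrawal ground in Section 5.5 also covers patients in these groups who were missed at screening.

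The cost is a protocol amendment with IRB approval and a revised screening form. Compared with screening on 5.2 as it stands, some patients would no longer be eligible, mainly older men and users of aspirin or anticoagulants, and enrolment of the 100 could slow slightly. Compared with what 2.3.1 already commits to, no intended participant is lost.
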